### Neurocognitive and structural brain imaging studies in prodromal samples

Neuroimaging and neurocognitive studies have attempted to find reliable psychosis high-risk biomarkers. Two recent meta-analyses at high risk for psychosis showed that high-risk subjects are already neurocognitively impaired relative to matched controls [36,37]. There was a high variability across individual studies, and no reliable neurocognitive biomarkers have adequate sensitivity and specificity for clinical application in individual cases. Across neurocognitive domains, such as executive function, verbal fluency, attention, visual and verbal memory, and working memory, effect sizes were small to medium. Available research confirms that psychosis high risk is characterized by widespread mild cognitive deficits at a level that is intermediate between healthy individuals and those diagnosed with schizophrenia [38] and comparable to those at familial risk [39]. Neurocognitive impairments in psychosis high risk predict longitudinal functioning [40]. The magnitude of neurocognitive deficits is greater in subjects with a psychosis risk state who will later transit to psychosis as compared to those who will not [36], supporting the existence of different psychosis high-risk endophenotypes [36]. Neuroimaging techniques have the potential to find true indicators of psychosis vulnerability [41]. Early studies employed structural imaging methods and focused on regions known to be affected in schizophrenic psychoses such as hippocampus [42,43] or anterior cingulate cortex [44]. Since then, a number of structural studies employing whole-brain methods such as voxel-based morphometry or region-of-interests methods have been published. As compared to matched controls, high risk individuals show significant alterations in regional gray matter volume regardless of whether they subsequently develop the disorder [45]. These alterations are particularly evident in prefrontal and temporolimbic areas [46]. The largest multicenter structural study conducted in UHR showed parahippocampal alterations predicting psychosis onset [45].

### Aims

The primary aim of the current study is to test the effect of a Prodromal Detection and Treatment program at the health care systems level. The study will investigate; 1) If the combination of information campaigns and detection teams modelled will help in identifying individuals at high risk of developing psychosis early, and 2) If a graded, multi-modal treatment program will reduce rates of conversion compared to the rates seen in follow-along assessments. The study will use the knowledge obtained and the treatment strategies developed from recent experimental studies, and test them out on the health care system level as a proof-of-concept study that intervention in the prodromal phase may lead to a reduction in the development of new cases. The endpoint or main outcome will be the rate of conversion to psychosis. The study will be conducted within a translational approach, comprising clinical and genetic sub-projects as well as an FMRI sub study at Stavanger University hospital, Norway done in close collaboration with health regions in Southern Norway. The aim of these sub-projects is to identify neurobiological indicators of psychosis vulnerability.

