## Abstract

**Background:**

Evidence has been accumulating that it may be possible to achieve prevention in psychotic disorders. The aim of the Prevention Of Psychosis (POP) study is to reduce the annual incidence of psychotic disorders in a catchment area population through detection and intervention in the prodromal phase of disorder. Prodromal patients will be recruited through information campaigns modelled on the Scandinavian early Treatment and Intervention in Psychosis (TIPS) study and assessed by low-threshold detection teams.

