**Methods/Design:**

The study will use a parallel control design comparing the incidence of first episode psychotic disorders between two Norwegian catchment areas with prodromal detection and treatment (Stavanger and Fonna) with two catchment areas without a prodromal intervention program (Bergen and Østfold). The primary aim of the current study is to test the effect of a Prodromal Detection and Treatment program at the health care systems level. The study will investigate: 1) If the combination of information campaigns and detection teams modelled will help in identifying individuals (age 13–65, fulfilling study inclusion criteria) at high risk of developing psychosis early, and 2) If a graded, multi-modal treatment program will reduce rates of conversion compared to the rates seen in follow-along assessments.

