### Prodromal treatment package

This will be modeled after practices tried out in the TIPS study as well as practices shown to influence risk of conversion in experimental studies and common to existing prodromal centers. The patients will participate in an individual 2 year follow-along containing the following elements:One-to-one monitoring of clinical status, symptom levels (prodromal and psychotic), risk profiles (suicidality, dangerousness), instrumental and social functioning;One-to-one case management to help deal with clinical, familial, social and vocational crises, needs and deficits;Omega-III fatty acids, in the form of 2g fish oils containing approx. 1.5 g Etyl-Eicosapentaeonic Acid/DHA with 80 mgs Vitamin E per day for 12 weeks;Individual cognitive behavioral therapy (CBT) to deal with social/cognitive distortions and deficits and to maintain real world investment (based on the EDIE II study) [49]. They will be offered 26 sessions of CBT within a six months period. The CBT sessions will be based on established cognitive models, be collaborative, problem orientated, formulation driven, normalizing, educational and time-limited with Socratic questioning/ guided discovery;Individuals that experience functional loss will in addition receive single-family psycho-education to inform patients and families about current problems, how to understand and cope with them, especially within the family [50,51];Anti-anxiety agents and anti-depressants will be available if the patient is so symptomatic that they otherwise would be prescribed these agents by their GPs;Antipsychotic medication will be available if the patient either enters the study with any SIPS positive symptom score at the level of 5, or if any positive prodromal symptom score(s) moves from a level of 3 or 4 to a 5. Use will be open labeled based on the patients’ current symptom profile. The type and dose of medication will be reviewed by an independent clinical practice safety monitoring board.

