### Questionnaires and interviews

Participants will be screened with the Structured Interview for DSM-IV (SCID) [52] /(Kiddie SADS for adolescents who are 13–17 years old) and the SIPS at study entrance. All participants will be followed with a symptomatic assessment (SIPS) done monthly for the first six months and then every three months for the last two years. The participant will be evaluated by a designated nevopsychological protocol at baseline, 12 and 24 month follow-up and offered to participate in a fMRI substudy. Assessors will not be part of the treatment teams.

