### Power calculation

There are no previous studies giving any clear suggestion of the number of high-risk individuals that can be recruited from a well-defined catchment area sample like the current, but previous studies in Melbourne indicate that around 20% of first episode patients have been in contact with the PACE clinic ([name], personal communication). Studies up to now give a conservative estimate of a 20% transition rate over the first two years for a non-treated high-risk sample and subsequently a 10% risk in the active treatment group. A power analysis has shown that in order to give an achieved significant reduction of transition rates in the study population with the proposed sample size for the two groups of a) 750 000 with predicted annually detection of 150 first-episode psychosis (FEP) (Bergen and Østfold) and b) 440 000 with annually predicted reduction to 90 FEP (Stavanger and Fonna) through prodromal detection and intervention, the study will have power of 88.9% to yield a statistically significant result.

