### The psychosis incidence study

The main outcome of the intervention will be the incidence of psychotic disorders in the participating areas. This will be assessed using the same research diagnostic criteria; in all participating areas over all study years.

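### The article names two different main outcomes, conversion among high-risk participants and psychosis incidence in the catchment areas, and its power statement does not settle which one decides the trial

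*Protocol article*

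**What the plan says.** Two sentences in the current text each fix the main outcome.

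- Aims: "The endpoint or main outcome will be the rate of conversion to psychosis". The second aim in the same section shows what conversion refers to: "If a graded, multi-modal treatment program will reduce rates of conversion compared to the rates seen in follow-along assessments". That is a rate among high-risk people who are enrolled and followed. Under Prodromal inclusion and exclusion criteria, these people live in the Stavanger and Fonna areas only.
- The psychosis incidence study: "The main outcome of the intervention will be the incidence of psychotic disorders in the participating areas". Under Incidence study inclusion criteria, cases come from all four areas.

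The Abstract sides with incidence. Its stated aim is to "reduce the annual incidence of psychotic disorders in a catchment area population through detection and intervention in the prodromal phase of disorder", and its design sentence reads "The study will use a parallel control design comparing the incidence of first episode psychotic disorders between two Norwegian catchment areas".

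The Power calculation draws on both. It begins with "a conservative estimate of a 20% transition rate over the first two years for a non-treated high-risk sample" and a 10% risk under active treatment, and describes the target as a lower transition rate. It then gives area populations with annual first-episode counts and one power figure, 88.9%.

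**The concern.** These are not two wordings of one endpoint. Conversion has enrolled high-risk people as its denominator and follow-along as its comparator. Incidence has area residents as its denominator and Bergen and Østfold as its comparator.

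The two can part company. The section on conversion in prodromal samples reports falling conversion rates at one clinic and suggests that changed referral sources may have brought in more false positives. This study recruits by public campaign and accepts self-referral. The conversion rate could therefore fall through dilution while the number of new psychosis cases stays the same. Treatment could also work in those enrolled and barely move area incidence if the programme reaches only a small share of future cases.

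If the results disagree, the article gives no basis for saying which one decides, so a reader cannot exclude that the choice was made after the data were seen.

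**Working it through.** **Side by side**

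| | Conversion (Aims) | Incidence (incidence study) |
|---|---|---|
| Who is counted | enrolled high-risk people | first-episode cases |
| Areas | Stavanger, Fonna | Stavanger, Fonna, Bergen, Østfold |
| Denominator | people enrolled | residents (440 000 and 750 000 in the Power calculation) |
| Comparator | follow-along | Bergen and Østfold |

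**Does the power figure show which outcome was meant?** Alpha and sidedness are not stated; I assume 0.05, two-sided unless noted. The formula is the usual normal approximation for two proportions:

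power = Φ{ [|p1 − p2| − 1.96·√(p̄(1 − p̄)(1/N1 + 1/N2))] / √(p1(1 − p1)/N1 + p2(1 − p2)/N2) }

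*As incidence.*

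1. Control areas: 150 / 750 000 = 20.0 per 100 000. Intervention areas: 90 / 440 000 = 20.45 per 100 000. The ratio is 1.02.
2. At the control rate, 440 000 people would yield 150 × 440 000 / 750 000 = 88 cases. The planned 90 is slightly above that, so it is no reduction per head.
3. For one year: |p1 − p2| = 0.45 × 10⁻⁵; 1.96 × pooled standard error = 5.29 × 10⁻⁵; denominator = 2.70 × 10⁻⁵. Φ(−1.79) = 3.7%. Five years of cases give 5.7%. One-sided, the figures are 7.1% and 10.3%. All of these are for a difference in the direction of the counts, which is higher incidence in the intervention areas.
4. Solving backwards, 88.9% needs about 54 annual cases in 440 000 (one year). The article does not state that number.

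*As conversion.*

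5. For 20% versus 10%, 88.9% power needs 257 people per group two-sided, or 208 one-sided. The article gives no number of high-risk participants to compare with this.
6. If 150 and 90 are read as group sizes for 20% versus 10%, power is 53% to 58% two-sided and 66% to 69% one-sided.

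No direct reading of the stated inputs returns 88.9%, so the power figure does not identify the outcome on which the study was sized.

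**How far can the outcomes diverge?** The Power calculation says that around 20% of first-episode patients in Melbourne had been in contact with the prodromal clinic there. Assume the same reach here, and the planned halving of conversion (20% to 10%) in those reached. Area incidence then falls by 0.20 × 0.50 = 10%, from 88 to 79.2 cases a year in 440 000. The same formula gives 11% power on one year's cases and 40% on five. Under these assumptions a treatment that does all it was planned to do would more likely miss than reach significance on incidence.

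**The case against.** The strongest reply is that the article leans one way. The Abstract's aim, its design sentence and the incidence section all name incidence. The second paragraph of the Background treats lower conversion as the route by which incidence would change. The Aims sentence follows directly on talk of the health care system and of fewer new cases, so it may be loose wording for new cases. Ranking of outcomes and multiplicity rules also commonly sit in an analysis plan, which is not shown. The lean is real and guides the fix. But the second aim, in the same section, ties conversion to treatment versus follow-along. The article also fixes the main outcome twice, differently, which is not the same as leaving it to another document.

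Several stronger readings are tempting and are not supported:

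- *Success can be declared on either outcome, so the false-positive rate is 1 − 0.95² = 9.75%.* No success rule or alpha is stated. The calculation also needs independent tests, yet converters in Stavanger and Fonna who meet the incidence criteria are themselves incident cases.
- *Conversion has no parallel control.* The Background has people allocated to follow-along or to treatment, while Overall design has recruits receive both yet also refers to treatment allocation. The text contradicts itself, and neither reading can be taken as settled.
- *Conversion is measured with the SIPS and incidence with other instruments.* The SIPS is scheduled as a symptom assessment; no section says that it ascertains conversion.
- *The outcomes move in opposite directions.* The documents support only that one can change while the other does not.
- *Follow-up for conversion is 30 months.* The schedule "done monthly for the first six months and then every three months for the last two years" can be read so, but the treatment section says "The patients will participate in an individual 2 year follow-along containing the following elements" and the Power calculation also uses two years. No analysis at 30 months is planned. This is schedule wording to reconcile, not a second horizon.

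**Conclusion.** The point holds. The Aims and the incidence section name different main outcomes, and the Power calculation mixes them under a figure that follows from neither. The article therefore does not fix which result decides the trial.

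The conflict itself rests on the text and needs no statistical assumption. So does the absence of a per-head reduction, 20.0 against 20.45 per 100 000. The power values rest on an assumed alpha of 0.05 and a normal approximation. The 10% fall in incidence also assumes that the Melbourne reach applies here. The divergence by dilution is a possibility that the article's own literature review raises; its effect on a treatment comparison would depend on the comparator, which is unclear. No error rate for this trial can be computed from what is shown.

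**What to change.** - In Aims and in The psychosis incidence study, name area-level incidence as the single primary outcome, which agrees with the Abstract's aim and design. Make conversion over two years, the horizon in the treatment and power sections, a secondary outcome.
- In Power calculation, restate the power for incidence alone, with the assumed rate in each pair of areas, the years of accrual, and alpha with its sidedness.
- Reconcile the Background (follow-along or treatment) with Overall design (both), so that the comparator for conversion is clear.
- Reconcile the assessment schedule in Questionnaires and interviews with the two-year follow-along.

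If the sponsor prefers conversion as primary, the Abstract's aim and design sentence must change instead, and a number of high-risk participants must be stated and justified.

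No new data are needed, but this is more than an edit of wording. The restated power may be much less favourable than 88.9%. Inclusion opened in March 2012, so the change should be dated and made before outcome data are analysed, with a statement that this was so.

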## Methods/Design

### Overall design

The current study will use a health service design modeled after the TIPS study, using the unique possibilities of the Norwegian catchment area based treatment systems. UHR patients from two areas (the catchment areas of Stavanger and Fonna) will be recruited through information campaigns and assessed by low-threshold detection teams. Recruited individuals will, after giving informed consent, receive structured follow-along by a designated case manager, and receive a multi-modal treatment package containing CBT, family work and Omega-III fatty acids and with the possibility for provision of antipsychotic medication only at imminent risk of conversion. Study personnel blind to treatment allocation will confirm this through a separate symptomatic evaluation.

### Information campaigns and detection teams

Each Prodromal Detection and Treatment site will implement a program building upon the combined experiences from the TIPS study and previous prodromal studies, consisting of Information Campaigns (IC) and Low Threshold Detection Teams (DT) [2]. Prodromal detection, like early psychosis detection, requires active outreach and recruitment using information campaigns and specialized detection teams. As demonstrated by the TIPS project, both elements are likely to be critical [47]. Given that the threshold pathology in the prodrome is likely to be more privately experienced and less publicly apparent, the IC must be intense, persistent, pervasive, and personal. The IC will use three concrete strategies:A)Teaching the public about early signs of severe mental illness, the importance of getting help early and the existence of the low threshold DTs;B)Provide targeted education programs for teachers and General Practitioner’s (GPs) about prodromal symptoms and the content and availability of the PDT program;C)Provide targeted education for clinicians in the specialized mental health services to learn them to recognize possible prodromal individuals.

Potential prodromal individuals in the PDT areas will be referred to a DT by health care providers, educators, or social service agencies or they can be self-referrals in response to the IC. Potential subjects will undergo a telephone and/or a face-to-face screen (Prodromal Questionnaire, PQ-B) [48]. Those who screen positive will be invited to an in-person eligibility and consent evaluation based on the SIPS interview.

### Prodromal treatment package

This will be modeled after practices tried out in the TIPS study as well as practices shown to influence risk of conversion in experimental studies and common to existing prodromal centers. The patients will participate in an individual 2 year follow-along containing the following elements:One-to-one monitoring of clinical status, symptom levels (prodromal and psychotic), risk profiles (suicidality, dangerousness), instrumental and social functioning;One-to-one case management to help deal with clinical, familial, social and vocational crises, needs and deficits;Omega-III fatty acids, in the form of 2g fish oils containing approx. 1.5 g Etyl-Eicosapentaeonic Acid/DHA with 80 mgs Vitamin E per day for 12 weeks;Individual cognitive behavioral therapy (CBT) to deal with social/cognitive distortions and deficits and to maintain real world investment (based on the EDIE II study) [49]. They will be offered 26 sessions of CBT within a six months period. The CBT sessions will be based on established cognitive models, be collaborative, problem orientated, formulation driven, normalizing, educational and time-limited with Socratic questioning/ guided discovery;Individuals that experience functional loss will in addition receive single-family psycho-education to inform patients and families about current problems, how to understand and cope with them, especially within the family [50,51];Anti-anxiety agents and anti-depressants will be available if the patient is so symptomatic that they otherwise would be prescribed these agents by their GPs;Antipsychotic medication will be available if the patient either enters the study with any SIPS positive symptom score at the level of 5, or if any positive prodromal symptom score(s) moves from a level of 3 or 4 to a 5. Use will be open labeled based on the patients’ current symptom profile. The type and dose of medication will be reviewed by an independent clinical practice safety monitoring board.

### Questionnaires and interviews

Participants will be screened with the Structured Interview for DSM-IV (SCID) [52] /(Kiddie SADS for adolescents who are 13–17 years old) and the SIPS at study entrance. All participants will be followed with a symptomatic assessment (SIPS) done monthly for the first six months and then every three months for the last two years. The participant will be evaluated by a designated nevopsychological protocol at baseline, 12 and 24 month follow-up and offered to participate in a fMRI substudy. Assessors will not be part of the treatment teams.

### Prodromal inclusion and exclusion criteria

Start of study inclusion is from March 1^st^ 2012, ending inclusion December 31^st^ 2016.

1) The patient is listed in the national register and residing in the catchment areas of: Stavanger and Fonna; 2) Between 13 and 65 years; 3) Meet diagnostic criteria for prodromal syndrome SIPS criteria [11]; 4) Does not meet current or life-time criteria for any psychotic disorder; 5) The symptoms are not better accounted for by an axis I, axis II or substance use disorder with the exception of schizotypal personality disorder (the presence of any of these disorders in itself is not an automatic reason for exclusion); 6) Does not use any antipsychotic medication currently and have not used antipsychotic medication (regardless of dosage) for more than four weeks lifetime; 7) No known neurological or endocrine disorders that may have caused the presenting psychotic symptoms; 8) The patient is not mentally retarded with an IQ below 70; 9) The patient must be able to understand and speak Norwegian; 10) The patient must be able to understand and sign an informed consent or assent for minors’ document.

